## Background

Necrotising enterocolitis (NEC) is among the most potentially devastating neonatal diseases and has a mortality of up to 33%, the most severe form (requiring surgery or resulting in death) affects about 5% of infants born at <30 gestational weeks^1^; survivors are at high risk of long-term health^2^ and developmental problems.^3 4^ Prevention of NEC has been identified as one of the most important research uncertainties in the field of preterm birth.^5^ The pathogenesis of NEC is incompletely understood, however a temporal association between red cell transfusion and the subsequent development of the disease is well described.^6 7^ This ‘transfusion associated NEC’ may be more severe^8^ with higher mortality.^9 10^ The mechanism thought to underpin this relationship links milk feeds and packed red cell transfusion to NEC through altered mesenteric blood flow and intestinal barrier function; this is supported by animal^11^
^12^ and human studies^13^
^14^
^15^. Understanding the link between NEC and blood transfusion is of particular importance given that almost all very preterm babies will have a red cell transfusion and many will receive multiple transfusions^16^.

Stopping milk feeds around the time of packed red cell transfusion is currently practised in some neonatal settings to reduce the risk of NEC, putatively by maintaining more physiological intestinal blood flow.^17^ This practice has not, however, been tested in an adequately powered randomised trial, and there are physiological reasons why stopping milk feeds in preterm infants may lead to harm. Interrupting enteral feeding prolongs the time taken to reach full milk feeds, which is associated with invasive infection^18^, and may paradoxically be associated with an increased risk of NEC 19. One small, single-centre randomised pilot trial has assessed withholding enteral feeds around red cell transfusion but was underpowered to detect a difference in NEC.^20^ A systematic review of observational studies^21^ identified seven historical control studies including 7492 preterm infants; these studies were at high risk of bias including regression to the mean and ascertainment bias. Pooled results found an association between withholding feeds in the peritransfusion period and a reduced risk of NEC. The authors concluded that adequately powered randomised controlled trials are needed to confirm these findings.

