There is considerable variation in current UK practice in relation to withholding enteral feeds during packed red cell transfusion in preterm infants: a 2011 survey of UK neonatal units (68% response rate) demonstrated that 35% of UK units routinely withheld enteral feeds during packed red cell transfusion.^22^

If withholding enteral feeds around the time of packed red cell transfusion reduces the risk of NEC, then implementing this simple practice will reduce the mortality and long-term complications of NEC. Conversely, if the safety of continued feeding can be demonstrated, this will facilitate increased and consistent feeding with breastmilk, which has well described short-term and long-term benefits.

NEC is rare and occurs at a higher incidence in the most preterm infants and so trials targeting NEC need a large number of very preterm infants, who are themselves rare. As a result, no previous trial has been powered to look at NEC and there is no intervention to prevent NEC supported by high-quality randomised evidence. Methologies that have been proposed to improve efficiency and recruitment into randomised trials include the use of simplified opt-out approaches to consent,^23^ and embedding trial processes into existing electronic patient record (EPR) systems.^24^

The objectives of this pilot trial are:

To determine whether a large multicentre trial addressing the following question is feasible: *among preterm infants (patient), does the practice of withholding enteral feeds around the time of blood transfusion (intervention), compared with continued enteral feeding around the time of blood transfusion (comparator), lead to a reduction in severe necrotising enterocolitis (outcome)?*
To determine whether clinical trial processes (identifying participants, randomisation and data collection) can be successfully integrated into existing neonatal EPR systems, and whether trial data can be extracted from routinely recorded clinical data held in the National Neonatal Research Database (NNRD).To determine whether using a simplified opt-out consent process is feasible and acceptable to parents and health professionals.

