### Outcomes

Feasibility outcomes:

Recruitment: proportion of infants <30 weeks of gestation admitted whose parents agree to trial involvement and the infant is randomised in the WHEAT trial.Retention: proportion of of recruited infants where outcome data are available up to the end of the follow-up period.Compliance: proportion of recruited infants who correctly received their allocated care pathway around all packed red cell transfusions between randomisation and 34+6 gestational weeks+days.Data completeness: proportion of missing data for each data item reported as a baseline characteristic or an outcome.Data accuracy: proportion of cases where the following data items are correctly recorded when compared with source data (clinical notes or EPR data).Severe NEC: all infants who had a diagnosis of non-severe NEC and a random sample of 25% of infants who did not have a diagnosis of NEC will have their source data verified to ensure that they do not meet the criteria for severe NEC; 25% was selected for pragmatic reasons.Spontaneous intestinal perforation.All-cause mortality.Central line associated blood stream infection.

Clinical outcomes:

All clinical outcomes will be assessed from randomisation to 40+0 weeks of gestation or neonatal unit discharge, whichever occurs first.

Severe NEC: histologically or surgically confirmed, or recorded in part 1 the death certificate. These infants will be identified as described in Battersby *et al*,^25^ which will include infants recorded as being transferred for surgerySpontaneous intestinal perforation: histologically or surgically confirmed, or recorded in part 1 the death certificate.All-cause mortality.Total duration of neonatal care in days: including all levels of care (intensive care, high dependency care, special care and ordinary care).Duration of any parenteral nutrition in days.Number of days with a central venous line in situ.Number of central line associated blood stream infections defined according to National Neonatal Audit Programme 2017 definition^26^
Growth: change in birth weight and head circumference for gestational age SD score.

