### Sample size

There is no predefined sample size for this pilot trial. Recruitment (absolute numbers and the rate) will be a primary outcome for the pilot trial. The estimated recruitment target for the pilot trial is up to 250, based on predicted infant throughput at participating neonatal units and assuming 65%–70% recruitment of eligible infants.

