### Statistical methods

The planned main WHEAT trial will be based on a superiority hypothesis; however, the pilot trial is not powered to detect any differences between the intervention arm (withholding feeds) and the comparator arm (continuing feeds).

Therefore, no formal statistical hypothesis testing will be conducted.

Continuous variables will be summarised using means and SD unless their distributions are skewed, in which case medians, 25th quartiles, 75th quartiles and the range (lowest and highest values) will be presented. Dichotomous variables will be presented as frequencies and percentages. In addition, 95% CIs will be presented for the feasibility outcomes. The recruitment rate will be reported for both arms combined, and retention and compliance rates will be reported separately by treatment arm in addition to both arms combined.

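### Accuracy of perforation, line infection and (less critically) death is a single overall proportion correct, which can stay high when rare events are missed; report sensitivity and positive predictive value

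*Protocol article*

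**What the plan says.** Under Outcomes, the protocol article defines data accuracy as the "proportion of cases where the following data items are correctly recorded when compared with source data". The first item is severe NEC. The others, run together in the extracted text, are "Spontaneous intestinal perforation.All-cause mortality.Central line associated blood stream infection".

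Severe NEC has its own verification rule: every infant with a non-severe NEC diagnosis is checked against source, as is "a random sample of 25% of infants who did not have a diagnosis of NEC". No verification set is stated for the other three items, and the word *cases* is not defined.

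Under Statistical methods the article adds that "95% CIs will be presented for the feasibility outcomes". It does not split accuracy by whether the event occurred, and it sets no accuracy threshold. The Design section names data accuracy among the primary feasibility metrics. It bears directly on the second objective, at the end of Background: "whether trial data can be extracted from routinely recorded clinical data held in the National Neonatal Research Database".

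**The concern.** These items are events that an infant either has or does not have, although line infection is also counted. If *cases* means infants, every infant who has no event and no recorded event counts as correctly recorded. When the event is rare, such infants make up nearly the whole denominator. The percentage then mostly reflects how rare the event is and says little about whether the database captures it.

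The pilot is meant to show whether routine records can supply trial outcomes, so the question that matters is how many true events reach the database. A high accuracy figure with a narrow interval could be read as reassurance on that question without having tested it. The rule for severe NEC shows that the authors had missed events in mind for that outcome. No equivalent is stated for the other three.

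**Working it through.** **Inputs**

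- Pilot size, from Sample size: "The estimated recruitment target for the pilot trial is up to 250". I use N = 250 and assume every infant is verified.
- Event rates for perforation, death and line infection: none given. I assume 2%, 5% and 10% to show the range. The nearest figure is for severe NEC, which is not one of the three items: "the most severe form (requiring surgery or resulting in death) affects about 5% of infants born at <30 gestational weeks".
- The article states no accuracy figure, so there is none to reproduce.

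**Formula**

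Let p be the prevalence, se the sensitivity and sp the specificity of the database against source.

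Agreement = p × se + (1 − p) × sp

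With no false positives (sp = 1) this becomes

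Agreement = 1 − p × (1 − se) = 1 − prevalence × miss rate

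Agreement therefore cannot fall below 1 − p however many events are missed. For a 2% item, the whole range from no capture to full capture is 98% to 100%.

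**Results at N = 250, no false positives, exact (Clopper-Pearson) 95% intervals**

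| Assumed rate | Events | Missed | Agreement | Sensitivity |
|---|---|---|---|---|
| 2% | 5 | 5 | 245/250 = 98.0% (95.4 to 99.3) | 0/5 = 0% (0 to 52) |
| 2% | 5 | 4 | 246/250 = 98.4% (96.0 to 99.6) | 1/5 = 20% (0.5 to 72) |
| 5% | 12 | 7 | 243/250 = 97.2% (94.3 to 98.9) | 5/12 = 42% (15 to 72) |
| 10% | 25 | 12 | 238/250 = 95.2% (91.8 to 97.5) | 13/25 = 52% (31 to 72) |
| 10% | 25 | 15 | 235/250 = 94.0% (90.3 to 96.6) | 10/25 = 40% (21 to 61) |

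**Where the effect stops**

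Taking 95% only as a convenient marker, agreement exceeds it when prevalence × miss rate is below 5%. The prevalence must then be below:

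- 0.05 / 1.0 = 5.0% if all events are missed;
- 0.05 / 0.8 = 6.25% if 80% are missed;
- 0.05 / 0.6 = 8.3% if 60% are missed;
- 0.05 / 0.5 = 10% if half are missed.

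At 10% prevalence, missing 13 of 25 events (52%) gives 237/250 = 94.8%. False positives lower agreement further: with sp = 0.98, p = 5% and 80% missed, it is 0.05 × 0.2 + 0.95 × 0.98 = 94.1%.

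**The other reading of *cases***

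If *cases* means recorded events only, the measure is TP / (TP + FP), where TP and FP are true and false positives. That is the positive predictive value. In the 5% row, 5 events are recorded and all are true, so accuracy would be 5/5 = 100% with 7 of 12 events missed. Missed events are hidden under this reading too.

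**The case against.** Several points on the other side have force.

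- **A blanket claim fails.** A reader might infer that a database missing most events would score above 95% on all three items. The documents do not support that. They give no event rates for these items, and the inference fails at a prevalence of 10% or more. In the 10% example that stays above 95%, fewer than half the events (48%) are missed.
- **No threshold or progression rule depends on accuracy.** The 95% marker is mine, and no stated decision goes wrong because a score is high. The harm is in interpretation.
- **The outcome in the planned main trial's question is protected.** Severe NEC has a targeted check, so it would go too far to say that the pilot cannot show routine data to be fit for trial outcomes. The gap concerns the other items.
- **Death is the weakest example.** Strength and limitations describes database records of death as already shown to be robust. Perforation and line infection are not in that list.
- **Line infection is not purely yes/no.** The clinical outcome is the "Number of central line associated blood stream infections", so an infant-level check alone would miss errors in the count.
- **A fuller protocol or analysis plan may split accuracy by event status.** It may, and the article's wording does not forbid it. The commitment to frequencies as well as percentages should also show how many records disagree, though not in which direction. But the definition of a primary feasibility outcome is fixed here as one proportion. The article's section on changes to the analysis touches accuracy only through the 25% sample for severe NEC.

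These points narrow the size and reach of the concern. They do not restore the single proportion as a measure of event capture.

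**Conclusion.** The point holds in a limited form. As defined, accuracy for perforation and line infection, and less critically for death, can stay high while many events are missed, provided the events are rare and false positives few. At assumed rates of 2% and 5% in 250 infants, agreement of 97% to 98% is compatible with sensitivity of 0% to 42%. At 10% or more, missing over half the events takes agreement below 95%, so the masking is weaker.

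The figures rest on assumed prevalences, perfect specificity, full verification, the upper recruitment figure and *cases* meaning infants. The conclusion that missed events go unseen survives the other reading of *cases*. Nothing here shows that the database does miss events. The planned measure would not reveal it clearly if it did. The change is worth making because it concerns a primary feasibility metric and costs little.

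**What to change.** For each item, report:

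- the number of source-confirmed events;
- sensitivity (the share of source-confirmed events that are recorded) with an exact 95% CI;
- positive predictive value (the share of recorded events confirmed at source) with an exact 95% CI;
- overall agreement as a secondary line only.

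Define *cases*, and state which infants are source-verified for perforation, death and line infection. If infants without a recorded event are only sampled, weight each missed event by the inverse of the sampling fraction. At 25%, for example, one missed event found stands for four. The interval must then allow for the sampling, since a plain exact binomial interval would no longer apply. For line infection, also compare the recorded and source counts per infant.

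If all infants are verified, this changes only the wording of the analysis and uses the same records. If they are not, it also needs a stated verification set and a weighted analysis. The drawback is wide intervals: 5/12 gives 15% to 72%, and 0/5 gives 0% to 52%. That is the precision a pilot with few events can offer on event capture, and the report should say so.

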**Trial registration number:**

ISRCTN registry ISRCTN62501859; Pre-results.

Strengths and limitations of this studyNecrotising enterocolitis (NEC) is a rare but potentially devastating neonatal disease, occurring predominantly in the most preterm infants. Neonatal trials to-date have not been adequately powered to detect realistic reductions in NEC.In this prospective, randomised pilot trial we will evaluate the feasibility of a data-enabled neonatal trial with processes embedded within an existing electronic patient record (EPR) system; accuracy and completeness of trial data will be validated at source.In this individually randomised, comparative effectiveness trial we will pilot opt-out consent and explore parent and health professional views of this approach in a nested qualitative study.We will evaluate the feasibility of EPR-embedded randomised comparative-effectiveness trials using a simplified opt-out consent for efficient, quicker and less resource burdensome neonatal trials at scale.

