## Methods

### Design

The WHEAT trial is a randomised controlled, unblinded, multicentre, pilot trial comparing two care pathways. The primary metrics of feasibility are recruitment, data completeness and data accuracy; clinical outcomes include mortality and NEC. Infants will be randomised with a 1:1 allocation ratio (using permuted blocks of variable size), stratified within neonatal unit by gestational age at birth and infant sex. Trial processes will be embedded within neonatal EPR systems and all outcome data will be extracted from data that are routinely recorded within the existing neonatal EPR systems (BadgerNet and BadgerEPR), and held in the NNRD.

The trial will recruit infants from neonatal units within two neonatal networks in England: Northwest London Neonatal Network and Southern West Midlands Neonatal Operational Delivery Network. Recruitment will be for 9 months (15 October 2018 to 30 June 2019), with data collection continuing for a further 3 months, until all trial infants have finished follow-up at 40+0 corrected gestational weeks or neonatal discharge if sooner.

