### Strength and limitations

The proposed trial has a number of strengths. The robustness of core NNRD data (birth weight, sex, length of stay and death) have been previously demonstrated for research purposes,^1 35 36^ this pilot trial will prospectively evaluate their accuracy and completeness for clinical trials. The trial will evaluate the feasibility of recruiting infants across two neonatal networks, including smaller neonatal units that do not traditionally recruit into neonatal randomised trials. Limitations include the unblinded nature of the trial and the use of a potentially subjective primary outcome, NEC. We endeavoured to mitigate against these through use of a previously validated, objective definition for NEC.^1^

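### The source-verification set stated for severe NEC contains only infants not recorded as severe NEC; recorded cases should be added so that false positives can be counted

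*Protocol article*

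**What the plan says.** All references are to the protocol article.

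- **Design** ranks the metric: "The primary metrics of feasibility are recruitment, data completeness and data accuracy".
- **Outcomes, Data accuracy** gives a general definition for four items, severe NEC first: "proportion of cases where the following data items are correctly recorded when compared with source data (clinical notes or EPR data)".
- Under severe NEC, the same section says who is checked: "all infants who had a diagnosis of non-severe NEC and a random sample of 25% of infants who did not have a diagnosis" of NEC. These infants "will have their source data verified to ensure that they do not meet the criteria for severe NEC". On the fraction it says only that "25% was selected for pragmatic reasons".
- **Outcomes, Clinical outcomes** defines severe NEC by histological or surgical confirmation or by part 1 of the death certificate. It adds that identification follows a cited paper and "will include infants recorded as being transferred for" surgery.
- **Changes to the statistical analysis described in the original protocol** repeats the 25% sample with the same purpose and does not mention recorded severe cases.
- The strengths-and-limitations box after the abstract says that "accuracy and completeness of trial data will be validated at source".
- **Strength and limitations**, in the Discussion, accepts that NEC may be a subjective outcome in an unblinded trial and offers as mitigation the "use of a previously validated, objective definition for NEC".

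**The concern.** A record can be wrong in two directions: a true severe case may be missed, or an infant may be recorded as severe without meeting the criteria. Both groups in the stated set are recorded negatives, and the stated purpose concerns missed cases only. The second kind of error is therefore not covered by the only verification rule given for this item.

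That error has a plausible route. The definition asks for confirmation at surgery, on histology or on the death certificate, while identification includes a recorded transfer for surgery, which is not in itself confirmation.

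What is at stake is the purpose of the pilot, which is to show whether routinely recorded data can carry the main trial's outcome. False-positive cases that the intervention cannot prevent dilute a treatment effect and raise the sample size needed. A pilot that looks only for missed cases gives no information on this.

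**Working it through.** **1. The plan's own figure.** The article gives no figure for the accuracy check. Its one calculable sample size is the Discussion's illustration for a main trial: 6% background rate, 25% relative reduction (so 4.5%), 90% power, two-sided 5%. The usual two-proportion formula gives 4,644 per arm, 9,288 in total, in agreement with the stated figure of over 9000. The point does not depend on it; it is used only in step 6.

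**2. Who is checked.** Inputs from the article: up to 250 infants (Sample size) and about 5% severe NEC (Background). Assumptions: 3% to 6% as a range for severe NEC, and 3% to 10% for non-severe NEC, which the article does not give.

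At 5% severe NEC, 250 × 0.05 = 12.5, taken as 12:

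| Group | Infants | Checked as written |
|---|---|---|
| Recorded severe NEC | 12 | 0 |
| Recorded non-severe NEC | 8 to 25 | 8 to 25 |
| No NEC | 230 to 213 | 58 to 53 (25%) |
| Total | 250 | 66 to 78 |

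Recorded severe cases number about 8 at 3% (7.5 rounded) and 15 at 6%.

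**3. What the stated set identifies.**
- *False-negative proportion among recorded non-cases:* estimable. Non-severe records are a census (weight 1) and the no-NEC sample has weight 1/0.25 = 4.
- *PPV:* (recorded severe cases confirmed) / (recorded severe cases). No recorded case is checked, so it could lie anywhere from 0% to 100%.
- *Overall accuracy:* if there are no false negatives, every unchecked severe record may be wrong or right, so the lower bound is (250 − S)/250, where S is the number of recorded severe cases, and the upper bound is 100%.
  - S = 8: 242/250 = 96.8%
  - S = 12: 238/250 = 95.2%
  - S = 15: 235/250 = 94.0%

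**4. What adding the recorded cases gives.** The verified total at 5% rises from 66–78 to 78–90. PPV becomes estimable. Exact (Clopper-Pearson) intervals:
- 12 of 12 confirmed: lower limit 0.025^(1/12) = 73.5%; interval 73.5% to 100%.
- 10 of 12 confirmed: 83.3%, interval 51.6% to 97.9%.

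**5. Why a combined figure needs weights.** As an illustration, take 12 non-severe records with 2 misclassified and 56 sampled no-NEC infants with none. Unweighted: (10 + 56)/(12 + 56) = 66/68 = 97.1%. Weighted: (10 + 4 × 56)/(12 + 4 × 56) = 234/236 = 99.2%. Both figures describe recorded non-cases only.

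**6. Why PPV matters later (illustration; the false-positive shares are assumptions).** Suppose false positives occur equally in both arms and the 25% reduction acts on true cases only.
- One sixth of the 6% false (1.0% false, 5.0% true): recorded rate in the other arm 1.0% + 0.75 × 5.0% = 4.75%. The same formula gives 13,678 infants, and 13,678/9,288 = 1.47.
- One twelfth false (0.5% and 5.5%): 0.5% + 0.75 × 5.5% = 4.625%, giving 11,180 infants.

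**The case against.** The strongest reply is that the general definition governs. It covers severe NEC, is not limited to recorded negatives, and is backed by an unqualified statement that trial data will be validated at source. On that reading recorded cases are checked anyway, and the text under severe NEC describes an additional search for missed ones. The article is also condensed, and the base verification rules may be in the supplementary protocol. This stands in part. A reader might infer that false positives are never sought; the documents do not support that, because nothing excludes recorded cases. But this is more than silence: the article fixes a set, its fractions and its purpose, and recorded cases are not in it.

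A reader might also infer that accuracy for severe NEC cannot be estimated at all. That goes too far: the false-negative side is estimable, and overall accuracy can be bounded.

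Three further replies hold. No section says the groups will be pooled without weights, so step 5 is a caution and not an error found. Whether a transfer alone is enough to count as a case depends on the cited paper, which is not at hand. And the pilot makes no comparison between arms and ties no decision to PPV, so no pilot result would be biased.

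The limited precision of the negative sample (none missed among 53 to 58 leaves an upper limit of 6.7% to 6.2%) is a separate matter: it concerns the size of that sample, and checking recorded cases would not change it.

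**Conclusion.** The point holds in limited form. The only verification set stated for severe NEC consists of recorded non-cases. Followed as written, it leaves about 12 recorded cases unchecked (8 to 15 at 3% to 6%), does not identify PPV, and bounds overall accuracy at about 95% to 100% at best. This rests on 250 infants, 5% severe NEC, no false negatives for the bound, and the stated set being the whole of the check. If the sponsor already verifies recorded cases under the general definition, the remedy is one clarifying sentence. Moderate importance; a cheap improvement, not a must-fix.

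**What to change.** - Add to the source-verified set all infants recorded as severe NEC, including those identified only by a recorded transfer for surgery. If they are already verified, say so.
- Report PPV among recorded cases with an exact 95% CI, separately from the false-negative proportion among recorded non-cases.
- Weight any combined accuracy figure by the inverse of the sampling fraction: 1 for every NEC record, 4 for the 25% sample.

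The cost is about a dozen further note reviews and a sentence or two in the plan. The added PPV will be imprecise and should be presented as such, and the reported accuracy may look slightly less favourable.
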